## Abstract

**Objective:**

Muscle weakness is prevalent in rheumatoid arthritis (RA), osteoarthritis (OA) and sarcopenia (SARC). Endurance exercises may improve mitochondrial function and oxidative capacity, while strength exercises are thought to stimulate myofibrillar protein synthesis. This study aims to compare the effects of strength and endurance exercise and explore the association between muscle characteristics and exercise outcomes in patients with RA, OA and SARC. We hypothesize that responses to endurance and strength exercises in patients with muscle weakness are influenced by intramuscular pathology including muscle morphology, mitochondrial function, and systemic inflammation, based on their disease pathology, potentially requiring personalized training schedules.

**Methods:**

This two-arm, parallel-group exploratory trial will enroll 69 patients (23 RA, 23 OA, 23 SARC), randomized to endurance (n = 35) or muscle strength exercises (n = 34), using minimization to balance disease type and gender. The 8-week intervention includes two supervised sessions per week using a controlled cable pulley device (Reforter™) and fitness equipment, plus one weekly home-based session. The primary outcome is isokinetic muscle strength (peak torque), measured with the Biodex system**®**. Secondary outcomes include muscle morphology, mitochondrial function, systemic inflammation and muscle endurance (by Biodex and 6 Minute Walk test). Muscle morphology will be assessed via 3D ultrasound imaging of the vastus lateralis. Mitochondrial function will be analyzed using high-resolution respirometry on muscle biopsies. Systemic inflammation will be measured using multiplex assays or ELISA on serum samples.

**Discussion:**

This study will explore differential responses to muscle endurance and muscle strength exercises in patients with RA, OA, and SARC, offering novel insights into the molecular mechanisms of muscle weakness. The findings may help identify potential mechanisms underlying variability in exercise response and provide effect size estimates to guide future confirmatory studies and more targeted exercise interventions.

**Trial registration:**

ClinicalTrials.gov NCT06480643 (date of registration28-06-24).

## Background

The number of people aged 60 years and older worldwide is expected to double over the next 30 years, with a triple- rise in those aged over 80, leading to a dramatic rise in the prevalence of age-related diseases such as (osteo)arthritis and sarcopenia (SARC, age-related low muscle quantity and quality) [1,2]. Individuals with rheumatoid arthritis (RA) and osteoarthritis (OA) experience a 25–50% reduction in muscle strength even despite treatment induced remission of arthritis in RA [3–5], while in sarcopenia, muscle strength declines by an estimated 10–40% [6]. Low muscle quantity and quality, defined as muscle mass, strength and performance, are associated with detrimental clinical outcomes with a high socioeconomic burden as loss of independence, increased fatigue and (co)morbidity [7–9] including falls and fractures [10,11]. Exercise training can counteract low muscle quantity and quality [11,12]. In addition, to improvements in muscle strength and physical performance, exercise induces multiple biological adaptations, including improved mitochondrial function and enhanced oxidative capacity, modulation of inflammatory pathways, and improved cellular stress responses such as reduced endoplasmic reticulum stress [13]. According to current evidence, exercise should be delivered frequently [14,15]. Although group-level comparisons of exercise modalities often report similar clinical outcomes [15], inter-individual variability suggests that muscle-specific characteristics may mediate differential responses to exercise [16].

In RA, muscle weakness cannot be attributed to a decrease in muscle mass alone but is most likely also linked to impaired mitochondrial functioning mediated by chronic systemic inflammation [3,17–19]. While muscle weakness is known to be present in OA patients, the underlying causes and the pathophysiology are still unclear [20]. In SARC, muscle weakness is associated with increased muscle wasting [21,22] and decreased sensitivity to protein synthesis (anabolic resistance) [23]. Endurance exercises, generally conducted at lower intensities (30% to 50% of 1RM) and performed to volitional failure, has been shown to improve local muscular endurance and stimulate mitochondrial adaptations, thereby increasing oxidative capacity within skeletal muscle [24–26]. In contrast, strength exercises, typically performed at intensities ranging from 60% to 90% of one-repetition maximum (1RM), [24] has been shown to promote myofibrillar protein synthesis [27–30]. The optimal loading strategy for combating muscle weakness in diseases with distinct muscle pathologies such as RA, OA, and SARC remains to be investigated.

Although RA, OA and SARC represent distinct clinical entities, they all present with reduced muscle strength and impaired physical functioning. The mechanisms underlying muscle weakness are, however, expected to differ between these conditions, ranging from chronic systemic inflammation in RA, to local joint-related and low-grade inflammatory processes in OA, and age-related muscle degeneration in sarcopenia [12]. These differences in underlying muscle characteristics may contribute to the substantial inter-individual variability observed in response to exercise and highlight the need for a better understanding of mechanism-based exercise approaches [16]. Therefore, this study aims to compare the effects of strength and endurance exercise and explore the association between muscle characteristics and exercise outcomes in patients with RA, OA and SARC. We hypothesize that responses to endurance and strength exercises in patients with muscle weakness are influenced by intramuscular pathology including muscle morphology, mitochondrial function, and systemic inflammation.

## Methods

### Study design

This study is a two-arm parallel-group exploratory trial. Participants will be randomized using a minimization procedure for allocation to either the muscle endurance or muscle strength exercise group (see section Randomization, blinding and allocation concealment). Assessments will be conducted at baseline and after 8 weeks (Fig 1) of intervention (post-treatment). Exercise training will be delivered at the outpatient clinic at Reade, center for rehabilitation and rheumatology in Amsterdam, as part of regular clinical care.

**Fig 1 pone.0356181.g001:**
[figure not shown]
Schedule of enrollment, intervention and assessments (SPIRIT).

The trial is designed according to the SPIRIT (Standard Protocol Items: Recommendations for Interventional Trials) guidelines [31] and principles of Good Clinical practices.

### Ethics approval and consent to participate

Ethical approval was gained from the University Medical Center Amsterdam Research Ethics Committee (ID study NL86908.018.24). All participants must provide consent to participate. In a telephone call investigators answer any questions about study and/or consent form. Consent is obtained via a paper form. The study will be conducted in accordance with the declaration of Helsinki principles.

### Trial registration

The study is registered at ClinicalTrials.gov NCT06480643.

### Declaration of generative AI and AI-assisted technologies in the writing process

During the preparation of this work, the authors used ChatGPT- 5.5 to assist with grammar and language editing. After using this tool, the authors reviewed and revised the text as necessary and take full responsibility for the final content of the publication.

### Participants

A total of 69 participants, aged 50–80 years, will be recruited for the study: 23 participants diagnosed with RA, 23 with OA, and 23 with SARC. The inclusion and exclusion criteria are presented in Table 1. Participants will be recruited through multiple channels, e.g., referral by rheumatologists, rehabilitation physicians.

**Table 1 pone.0356181.t001:** Inclusion and exclusion criteria.

Inclusion Criteria
**For all patients:**
Age 50–80 years
Willingness and motivation to exercise
Low muscle strength represented by hand grip strength (HGS) <27 kg (males) and <16 kg (females). If HGS is not possible due to pain or joint deformity, use chair stand test (>15s or inability without arms) [56]
Gait speed >0.8 m/s to exclude severely disabled patients [56]
**RA patients:**
Diagnosed with RA according to EULAR/ACR criteria [57]
Disease activity score (DAS28) 2.6–5.6 (EULAR criteria), de novo or despite DMARD therapy
Stable disease (no flare/change in medication) ≥3 months
No corticosteroid use in the last 3 months
Disease duration >1 and <15 years

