**Exclusion criteria**
BMI < 18 or >35 kg/m²
Contraindications for exercise based on the physical activity readiness questionnaire (PAR-Q) or history of severe heart conditions (e.g., heart failure, MI < 3 months, other cardiac diseases)
Use of beta-blockers during intervention
Neurological, cachectic, inflammatory diseases or co-morbidities affecting muscle quality (e.g., MS, ongoing cancer treatment, radiotherapy/chemotherapy in last 6 months, hyperthyroidism, diabetes type 1/2, long COVID)
Participation in regular high-load training (>2x/week) within 2 months before enrollment
Recent ligament/muscle tears or injuries (<6 months)
Use of performance-enhancing drugs or supplements affecting muscle mass (e.g., protein powder)
Inability to schedule exercise therapy
Insufficient Dutch language skills or no informed consent

ACR American College of Rheumatology, CRP C-reactive protein, DMARD Disease Modifying Anti-Rheumatic Drug, EULAR European League Against Rheumatism, MS multiple sclerosis, OA Osteoarthritis, PARQ Physical Activity Readiness Questionnaire, RA Rheumatoid arthritis, SARC Sarcopenia.

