i) Muscle morphology: 3D US (Affiniti 30 Ultrasound system of Philips, Bothell US) of the vastus lateralis muscle of the index knee will be used to quantify volume, muscle belly length (ℓm), muscle fascicle length (ℓfasc), physiological cross-sectional area (PCSA), tendon length (ℓt), and muscle-tendon complex length (ℓm + t) [38] of the vastus lateralis. Muscle volume is measured between the origin and distal end of the muscle belly using manual segmentation of the anatomical cross-sections and interpolation in custom software. Average fascicle length (ℓfasc) and pennation angles (αfasc) are estimated. A pennation angle is the angle between the longitudinal axis of the entire muscle and its fibers. PCSA is calculated by dividing muscle volume by ℓfasc.ii) Mitochondrial function: HRR will be used to measure mitochondrial energy production (i.e., mitochondrial oxidative capacity) with the Oxygraph-2k high-resolution respirometer (Oroboros Instruments, Innsbruck, Austria), [39]. In brief, mitochondrial function will be assessed with permeabilized muscle fibers originating from the muscle biopsy. The biopsy will be performed at the mid-section of the vastus lateralis of the quadricep muscle under local anesthesia (2–3 mL of 1% xylocaine), using a Bergström needle modified for manual suction. A small incision (~1 cm) will be made through which the biopsy is retrieved, and closed with skin glue or, if needed, sutures (Donati stitch). Part of the biopsy will be mechanically separated under a microscope to expose individual muscle fibers, followed by gentle teasing with fine forceps to improve substrate accessibility. This physical permeabilization step ensures that the sarcolemma is disrupted while preserving mitochondrial structure and function, allowing direct measurement of mitochondrial respiration using the Oxygraph system. Fibers will be transferred to the Oxygraph chambers and mitochondrial oxygen consumption will be continuously measured while performing a substrate-inhibitor-uncoupler-titration protocol. This protocol involves sequential addition of glutamate, malate, and pyruvate to assess complex I supported leak respiration, followed by ADP to stimulate coupled oxidative phosphorylation (OXPHOS) via complex I (NADH-linked), cytochrome *c* to test for outer mitochondrial membrane integrity, succinate to assess complex II supported respiration (Succinate-linked), FCCP to reveal total uncoupled electron transport system (ETS) capacity, rotenone to inhibit complex I, and finally antimycin A to inhibit complex III and reveal residual oxygen consumption. Systemic inflammation: blood will be withdrawn for investigation of blood-biomarkers for systemic inflammation (IL-6; IFN-γ; IL-17; IL-2; IL-4; IL-10 and TNF-α). Serum will be sampled from all participants and analyzed with multiplex cytokine analysis or ELISA (BD™ Cytometric Bead Array (CBA) Human Th1/Th2/Th17 CBA Kit, BD Biosciences, San Jose, CA, USA) to identify the cytokines that are differentially expressed in the RA, OA, and SARC patients. The following general inflammation markers will be assessed in addition to that: C-reactive protein (CRP) and erythrocyte sedimentation rate (ESR).

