
Other measures: To enable in-depth characterization of the study participants the following variables will be collected.

a. Patient characteristics: Sociodemographic and lifestyle characteristics will be assessed using a standardized questionnaire, including age, gender, height, weight, educational level, employment status, marital status, smoking and alcohol use (including duration), symptoms, and use of walking devices. Comorbidity will be assessed using the Cumulative Illness Rating Scale (CIRS) [40], administered through a semi-structured interview. Information on current medication use will be obtained from the participant’s medical record. Protein intake will be assessed using a 24-h dietary recall conducted by a trained researcher. Protein intake (g/day) will be calculated using the Netherlands Nutrition Centre database.b. Anthropometrics: Body composition will be assessed using direct-segmental multi-frequency bio-electrical impedance analysis (DSM-BIA) (Biospace Co, Korea). DSM-BIA has been validated for assessing segmental and whole-body composition against dual energy X-ray absorptiometry (DXA) [41]. Muscle mass is expressed as SMM (kg), SMM index (SMI, kg/m^2^) by dividing SMM (kg) by height squared (m^2^) [30], relative SMM (%) by dividing SMM (kg) by body weight (kg)*100, ALM/height^2^ (kg/m^2^) by dividing ALM (kg) by height squared (m^2^) and fat free mass (%).c. Disease characteristics: diagnosis will be obtained from the participant’s medical record; Radiologic severity of osteoarthritis will be assessed using Kellgren and Lawrence grade (K&L) [42].d. Performance: handgrip strength will be assessed with a JAMAR**®** Dynometer (Patterson Medical, UK) [43,44]. Participants will be seated with elbows flexed at 90 degrees, shoulders adducted and forearms in a neutral position without support. They will be instructed to squeeze the dynamometer maximally three times per hand, alternating between the right and left sides. The highest recorded value (kg) will be reported; Short Physical Performance Battery (SPPB test) [45]. The SPPB assesses lower extremity function through three components i) Balance Test: Participants perform progressively challenging standing positions (feet together, semi-tandem, and full tandem stance) for up to 10 seconds each. ii) Gait Speed Test: Walking speed is measured over a 4-meter course. iii) Chair Stand Test: Participants complete five timed chair rises without using their arms for support. The time to complete the five repetitions will be recorded in seconds. The total SPPB score (0–12) reflects overall lower limb function, with higher scores indicating better performance.e. Patient-Reported Outcome Measures (PROMs) will be measured with online questionnaires: Numeric Rating scale pain (0–10) [46], PROMIS® short forms regarding fatigue (8a) version 1.0, physical function (8b) version 2.0, ability to participate in social roles and activities (8a) version 2.0 [47]. FitMáx© survey [48] is a questionnaire consisting of three single answer questions, about the maximum capacity of walking (scale from 0–13), climbing stairs (scale 0–10) and cycling (scale 0–11). By adding the participant’s sex, age and BMI, the FitMáx© model estimates the maximum oxygen uptake, expressed in ml/kg/min [48,49].

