#### 2. Secondary outcome (Associations between muscle characteristics and exercise response).

i) Linear regression analyses will be conducted for each characteristic, e.g., muscle morphology (marker: DSM-BIA, physiological cross-sectional area and pennation angle), mitochondrial function (marker: Basal respiration; Leak respiration; NADH-linked respiration, Succinate-linked respiration, Maximal Oxidative Capacity; Maximum uncoupled respiration), and inflammation (markers: IL-6; IFN-γ; IL-17; IL2; IL-4; IL-10 and TNF-α). The change in muscle strength (T1 – T0) will be the dependent variable, and each muscle characteristic will serve as the independent variable.ii) To explore whether associations between muscle characteristics and exercise response differ by exercise modality, models will be extended by including exercise group and interaction terms (muscle characteristic × exercise group). Given the exploratory nature of the study and the limited sample size, these analyses are intended to identify potential signals rather than provide definitive evidence of effect modification. Interaction estimates will be interpreted cautiously, with emphasis on estimated effect sizes and 95% confidence intervals rather than statistical significance testing.iii) Adjusting for covariates. All models will be adjusted for the minimization factors (gender and disease type) and prespecified covariates (age and BMI). Given the exploratory nature of the study and the available sample size, the number of covariates will be restricted to reduce the risk of model overfitting..iv) Aforementioned steps will be repeated with other clinical outcomes (isokinetic muscle endurance, 6MWT, SPPB physical function and pain) as the dependent variables to address the secondary objective of the study.

Missing data will be addressed using the Multivariate Imputation by Chained Equations (MICE) method when data were assumed to be Missing Completely at Random (MCAR) or Missing at Random (MAR). Variables with substantial missingness (>30%) or data deemed Missing Not at Random (MNAR) will be excluded. Analyses on imputed data will be compared with the original dataset to assess consistency.

Analyses will be based on the intention-to-treat principle (ITT), in which data of all participants will be analyzed according to group assignment. In addition, per-protocol analysis will be performed including only those participants that performed 80% or more sessions.

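### Serum IL-6 and TNF-α are analysed as inflammation markers without separating RA patients on drugs directed at those cytokines, so the results for these two markers may be distorted

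*Protocol article*

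**What the plan says.** **Entry.** Under RA patients, Table 1 accepts "Disease activity score (DAS28) 2.6–5.6 (EULAR criteria), de novo or despite DMARD therapy". The table footnote expands the abbreviation only generically, as "DMARD Disease Modifying Anti-Rheumatic Drug", so conventional, biologic and targeted agents are not told apart. The other RA drug conditions are "Stable disease (no flare/change in medication) ≥3 months" and "No corticosteroid use in the last 3 months". The general exclusion list names beta-blockers and substances that affect muscle, but no cytokine-directed drug.

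**Role of the markers.** Outcome measures states that "blood will be withdrawn for investigation of blood-biomarkers for systemic inflammation (IL-6; IFN-γ; IL-17; IL-2; IL-4; IL-10 and TNF-α"; the list ends there. One stated purpose of the assay is "to identify the cytokines that are differentially expressed in the RA, OA, and SARC patients".

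**Models.** Data analysis plan, item 2, regresses change in strength on each marker. It then adds a marker-by-exercise-group interaction, and repeats these steps for muscle endurance, 6MWT, SPPB physical function and pain. On covariates it says: "All models will be adjusted for the minimization factors (gender and disease type) and prespecified covariates (age and BMI". It explains that the covariate list is kept short to limit overfitting.

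**Medication.** Outcome measures says "Information on current medication use will be obtained from" the medical record. The only use given for it is in the opening paragraph of the Data analysis plan, among the characteristics to be described.

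**The concern.** The trial's hypothesis is that systemic inflammation, among other muscle and disease features, shapes the response to exercise. The Discussion defends the wide range of RA disease activity on the ground that it lets the effect of inflammatory activity be examined. Both uses need the serum marker to track disease inflammation.

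A drug that acts on a cytokine or its receptor can disturb the measured level of that cytokine. The level is then partly a record of the prescription. Since the association models adjust for disease type, the slopes rest on spread within each disease, and RA is the group in which such drugs would be found. The comparison of cytokines between diseases has no protection at all, because any drug effect becomes part of the RA difference.

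At stake is the reading of two marker analyses that are meant to generate signals for later trials.

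**Working it through.** The plan gives no figure on this point, so there is none to reproduce. The check has two parts.

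**1. Does anything in the plan separate drug effect from disease effect?**

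- *Eligibility:* no. Untreated and DMARD-treated RA patients enter the same group, with no class limit.
- *Three months of stable medication:* this limits change over time. A steady drug effect on the baseline level remains.
- *No recent corticosteroids:* this deals with one drug class only.
- *Disease type as covariate:* this removes mean differences between RA, OA and SARC, but not the spread between treated and untreated patients within RA.
- *Medication record:* collected, but used only for description.

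**2. How much could it matter? (illustration under assumptions)**

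Inputs from the document: 23 RA patients enrolled; 60 analysed in all, or 60/3 = 20 per disease if losses are equal. Inputs that are assumed, because the document does not give them: the share *f* of RA patients on the drug class matching the marker (10–50%), and the shift *s* that the drug causes in that marker (1–3 within-disease SD). On these shares, 20 × 0.10 = 2 to 20 × 0.50 = 10 analysed patients would be affected.

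Let the marker be M = D + sB. D is the disease signal, with SD 1 in each disease. B is 1 for users of the matching drug and 0 otherwise, and is unrelated to D. Response depends on D with slope β.

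- RA alone: Var(M) = 1 + s²f(1−f) and Cov(M, D) = 1, so the fitted slope is β / [1 + s²f(1−f)].
- Three equal groups with disease type in the model: only a third of the within-disease variance is inflated, so the slope is β / [1 + s²f(1−f)/3].

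At the extremes:

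- f = 0.1, s = 1: s²f(1−f) = 0.09; RA alone 1/1.09 = 0.92; pooled 1/1.03 = 0.97.
- f = 0.5, s = 3: s²f(1−f) = 2.25; RA alone 1/3.25 = 0.31; pooled 1/1.75 = 0.57.

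Fraction of the true slope that remains:

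| f | s | RA alone | Pooled |
|---|---|---|---|
| 0.1 | 1 | 0.92 | 0.97 |
| 0.1 | 2 | 0.74 | 0.89 |
| 0.1 | 3 | 0.55 | 0.79 |
| 0.3 | 1 | 0.83 | 0.93 |
| 0.3 | 2 | 0.54 | 0.78 |
| 0.3 | 3 | 0.35 | 0.61 |
| 0.5 | 1 | 0.80 | 0.92 |
| 0.5 | 2 | 0.50 | 0.75 |
| 0.5 | 3 | 0.31 | 0.57 |

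The planned models pool the diseases, so the last column applies to them. If drug use is balanced between arms, the slope shrinks by the same factor in each arm, and so does the interaction.

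For the cross-disease comparison, the RA mean moves by f × s: from 0.1 × 1 = 0.1 SD to 0.5 × 3 = 1.5 SD, in whichever direction the drug moves the assay.

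**The case against.** **The mechanism is not in the document.** The protocol names no biologic or cytokine-directed agent and does not say how its assay behaves under one. This stands in part. The number of patients, and the direction and size of any shift, cannot be taken from the text. But the entry rule leaves such drugs open, and that a drug aimed at a cytokine can disturb its serum level is general subject knowledge. The point claims no more than that.

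**The covariate list was kept short on purpose, and sensitivity analyses are often left to an analysis plan.** The reason for a short list is sound, and the fix adds no covariate. But the covariate set is stated for all models, so it is a choice the article makes and not a gap.

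**The analyses are labelled hypothesis-generating.** This limits how serious the point is. It does not answer it, because a wide confidence interval shows imprecision and does not show that a marker partly measures a drug.

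**Stronger readings that the documents do not support.** A reader might infer that drug effects could create or reverse an association. The calculation shows attenuation only. Systematic creation or reversal would need drug use to be related to training response, for which the document gives no evidence. Leverage from a few extreme values is possible, but in a sample this small that holds for any cytokine. Nor does the plan say that the markers enter untransformed; it states no scale. A reader might also add users of both drug classes together, but each marker model is affected only by users of its own class. Finally, minimisation on disease and gender, with random allocation, should balance drug use between arms in expectation, so there is no case that the randomised comparison is biased.

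**Conclusion.** The point holds in a limited form. The plan admits RA patients on any DMARD, treats IL-6 and TNF-α as inflammation markers, fixes a covariate set that cannot separate drug from disease, and uses the medication record only descriptively. For users of a matching drug, the level may reflect treatment as well as inflammation. The plainest result is a weakened slope: 0.97–0.57 of its true value in the pooled models under the assumed ranges. The RA mean in the cross-disease comparison would also shift, in an unknown direction.

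These sizes rest on assumed shares and shifts, and on drug use being unrelated to the disease signal and to response. If no users of such drugs enrol, there is no effect. Two of seven cytokines are concerned, in exploratory secondary analyses. It would go too far to conclude that the inflammation analyses as a whole are invalid, or that the primary peak-torque comparison or the morphology and mitochondrial models are affected.

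**What to change.** Before the marker analyses begin:

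1. From the medication record already collected, classify each RA patient at baseline as on a TNF-directed agent, an IL-6-pathway agent, or neither, and report the counts.
2. Prespecify that the TNF-α association models (including the interaction and the repeats for other outcomes) are also run without users of TNF-directed agents, and the IL-6 models without users of IL-6-pathway agents. Do the same for the comparison of these two markers across RA, OA and SARC.
3. Report the restricted results beside the all-patient results. Do not interpret an IL-6 or TNF-α association as inflammation-related unless the estimates and confidence intervals are consistent in both.

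Eligibility, treatment and all other analyses stay as they are. The cost is one derived variable and a rerun of the analyses for two markers. Precision in the restricted models falls slightly: dropping 2 to 10 of 60 patients widens intervals by about √(60/58) = 1.02 to √(60/50) = 1.10, if residual and marker spread are otherwise unchanged.
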